#### **8.6.2.8 Hs-CRP**

Hs-CRP values are assessed at Baseline, Week 2, Week 4, Week 8, Week 12, Week 14, Week 16, Week 20 and Week 24.

Hs-CRP values which are recorded as <LLQ (i.e <0.10 mg/L) will be set to be half the value of the LLQ for these values (i.e 0.05 mg/L) for analysis purpose.

To test hs-CRP, the data will be log transformed prior to using a MMRM including as detailed in section 8.6.1.2. The results will be back-transformed to be presented in terms of adjusted least-squares (LS) geometric means, and ratios in LS geometric means together with 95% CIs and p-values.

If the data suggest that either endpoint is normally distribution rather than log-normally distributed then the analysis will be performed on the change from baseline without log-transformation.

The CRP assessments as well as the corresponding ratio to baseline will also be summarized descriptively by treatment group and visit for Part A and Part B.

The hs-CRP analysis will also be repeated, only including subjects with a baseline hs-CRP >ULN (5mg/L).

#### **8.6.2.9 ACR Components**

For all the continuous components which make up the ACR as well as MMRM analysis, they will be summarized by visit, treatment arm and Part.

For Part A and B there will also be a Last Observation Carried Forward (LOCF) summary of the ACR components to present the absolute, change from baseline and percent change from baseline by the randomized treatment arm. All missing data will be imputed using LOCF and subjects who completed the study at Week 12 due to country-specific protocol requirements (US participants) or subjects who switched arm at Week 12 will have their Part B scheduled visits be imputed with LOCF from their Week 12 visits.

### **8.6.3 Analysis of Key Secondary Efficacy Endpoints**

For the key secondary endpoints, summaries and analyses will be performed using the FAS.

In addition, for the key secondary dichotomous endpoints, a sensitivity analysis will be performed using the FAS. Summaries of part B will be performed using the FAS-B population.

#### **8.6.3.1 American College of Rheumatology 20 Clinical Response**

A key secondary endpoint is the proportion of ACR20 responders at Week 12 compared with baseline.

ACR20 response criteria is defined as:

- ACR20 Responder: *participant who had improvement in the ACR response criteria  $\geq 20\%$ ;*
- ACR20 Non-responder: *Otherwise.*

ACR20 response is:

- At least a 20% improvement in TJC68;
- At least a 20% improvement in SJC66;

At least a 20% improvement in at least 3 of the following 5 variables:

- PtAAP;
- PtGADA;
- PhGADA;
- HAQ-DI;
- hs-CRP.

ACR20 will be analysed using the same methods as used for ACR50.

### **8.6.3.2 Psoriasis Area and Severity Index 90**

A key secondary endpoint is change from baseline in PASI90 at Week 12 in the subgroup of participants with psoriasis [PsO] involving at least 3% body surface area [BSA] at baseline. This is expected to be between 50% and 67% of the FAS.

The PASI is a validated tool to dynamically assess PsA severity.

The PASI score is an established measure of clinical efficacy for PsO medications, which provides a numeric scoring for the participant's overall PsO disease state, ranging from 0 to 72. It is a linear combination of percent of surface area of skin that is affected and the severity of erythema, infiltration and desquamation over 4 body regions (Head, Trunk, Upper extremities, Lower extremities).

These correspond to 10%, 30%, 20% and 40% of the total body area respectively.

The area of psoriatic involvement of these 4 areas (Ah, At, Au, and Al) is given a numerical value:

- 0 = No involvement;
- 1 = <10%;
- 2 = 10% to <30%;
- 3 = 30% to <50%;
- 4 = 50% to <70%;
- 5 = 70% to <90%;
- 6 = 90% to 100% involvement.

The signs of severity, erythema (E), infiltration (I), and desquamation (D) of lesions are assessed using a numeric scale 0 to 4 where 0 is a complete lack of cutaneous involvement and 4 is the

severest possible involvement; scores are made independently for each of the areas, h, t, u and l and represent a composite score for each area.

An illustration of judging erythema follows:

- 0 = No erythema;
- 1 = Slight erythema;
- 2 = Moderate erythema;
- 3 = Striking erythema;
- 4 = Exceptionally striking erythema.

The PASI score is calculated according to the following formula:

$$\text{PASI} = 0.1(\text{Eh} + \text{Ih} + \text{Dh})\text{Ah} + 0.3(\text{Et} + \text{It} + \text{Dt})\text{At} + 0.2(\text{Eu} + \text{Iu} + \text{Du})\text{Au} + 0.4(\text{El} + \text{Il} + \text{Dl})\text{Al}$$

PASI90 is defined as an improvement of 90% or more in the PASI from baseline score.

The PASI90 will be assessed at Baseline, Week 4, Week 8, Week 12, Week 16, Week 20 and Week 24, but the key secondary endpoint is the assessment at Week 12.

The null hypotheses to be tested are that the proportion of PASI90 responders at Week 12 are not different for the following comparisons:

- sonelokimab 120 mg Q2W versus placebo
- sonelokimab 60 mg Q2W versus placebo
- sonelokimab 60 mg Q4W versus placebo

To test these hypothesis, a logistic regression will be used as detailed in section 8.6.1.1. This analysis will also be conducted for Week 2, 4 and 8.

The same sensitivity as for the primary endpoint will be presented and the same graphs and descriptive statistics will also be displayed for Part A and Part B.

## 8.6.4 Analysis of Other Secondary Efficacy Endpoints

For the other secondary endpoints, no confirmatory statistical testing will be performed, but statistical analyses may be used for exploratory proposes.

FAS will be used for all other secondary endpoints analysis. Summaries of part B will be performed using the FAS-B population.

### 8.6.4.1 American College of Rheumatology Clinical Response (ACR20/50)

Other secondary endpoints are:

- Proportions of ACR20 responders over time.
- Proportions of ACR50 responders over time.

ACR20 and ACR50 response criteria are defined in [section 8.6.3.1](#) and in [section 8.6.2.1](#) respectively.

A Non-responder imputation method will be used for all missing data as detailed in [section 7.3.1](#)

The ACR20/50 will be assessed at Week 2, Week 4, Week 8, Week 12, Week 14, Week 16, Week 20 and Week 24. Only Part A will be included in logistic regression analysis.

The exploratory null hypothesis to be tested are that the proportion of ACR20/50 responders at each time point in Part A are not different for the comparisons of interest for Part A. For exploratory purposes, the comparisons of interest will be:

- sonelokimab 120 mg Q2W versus placebo
- sonelokimab 60 mg Q2W versus placebo
- sonelokimab 60 mg Q4W versus placebo

ACR20/50 responders will be also summarized for all weeks for Part A, Part B and will be displayed by treatment group and visit as described in section 8.1.

### 8.6.4.2 American College of Rheumatology 70 Clinical Response (ACR70)

Other secondary endpoint include the proportion of ACR70 responders over time.

ACR70 response criteria is defined as:

- ACR70 Responder: *participant who had improvement in the ACR response criteria  $\geq 70\%$ ;*
- ACR70 Non-responder: *Otherwise.*

ACR70 response is:

- At least a 70% improvement in TJC68;
- At least a 70% improvement in SJC66;
- At least a 70% improvement in at least 3 of the following 5 variables:
  - PtAAP;
  - PtGADA;
  - PhGADA;
  - HAQ-DI;
  - hs-CRP.

The exploratory null hypotheses to be tested are that the proportion of ACR70 responders at each time point are not different for the comparisons of interest for Part A, a logistic regression will be performed as described in section 8.6.1.1. For exploratory purposes the comparison of interest will be:

- sonelokimab 120 mg Q2W versus placebo
- sonelokimab 60 mg Q2W versus placebo
- sonelokimab 60 mg Q4W versus placebo

ACR70 responders will also be summarized descriptively by treatment group and visit for Part A and Part B.

### 8.6.4.3 Psoriasis Area and Severity Index (PASI75/90/100)

Other secondary endpoints include the proportion of PASI75/90/100 responders over time.

PASI is derived as detailed in section 8.6.3.2. PASI75/90/100 are defined as an improvement in PASI score of 75%, 90% and 100% respectively.

The exploratory null hypotheses to be tested are that the proportion of PASI75/90/100 responders at each time point are not different for the comparisons of interest for Part A, a logistic regression will be performed as described in section 8.6.1.1. For exploratory purposes the comparison of interest will be:

- sonelokimab 120 mg Q2W versus placebo
- sonelokimab 60 mg Q2W versus placebo
- sonelokimab 60 mg Q4W versus placebo

PASI75/90/100 responders will also be summarized descriptively by treatment group and visit for Part A and Part B.

#### **8.6.4.4 Minimal Disease Activity**

Other secondary endpoints include the proportion of patients with minimal disease activity at Week 12.

Criteria for assessing minimal disease activity, listed below, covering all of the domains of the disease have been developed to determine whether the participant has reached minimal disease activity based on key outcome measures in PsA. Minimal disease activity is defined as meeting 5 of the 7 following criteria:

1. TJC68  $\leq 1$ ;
2. SJC66  $\leq 1$ ;
3. PASI  $\leq 1$  or PsO affecting  $\leq 1\%$  of BSA;
4. PtAAP  $\leq 15$  on a 0 to 100 VAS;
5. PtGADA  $\leq 20$  on a 0 to 100 VAS;
6. HAQ-DI  $\leq 0.5$ .
7. Leeds Enthesitis Index (LEI)  $\leq 1$

The null hypotheses to be tested are that the proportion of responders at Week 12 are no different for the following comparisons:

- sonelokimab 120 mg Q2W versus placebo
- sonelokimab 60 mg Q2W versus placebo
- sonelokimab 60 mg Q4W versus placebo

To test the hypotheses, a logistic regression will be used as detailed in section 8.6.1.1. Descriptive summaries by treatment group and visit will also be displayed for Part A and Part B. An LOCF/NRI analysis by visit similar to in section 8.6.2.1 will also be displayed for all scheduled visits in Part A and B.

#### **8.6.4.6 Leeds Enthesitis Index (LEI) and Spondyloarthritis Research Consortium of Canada Enthesitis Index (SPARCC)**

The LEI is a validated enthesitis index which uses 6 sites for evaluation of enthesitis (lateral epicondyle humerus [R/L], Achilles tendon insertion [R/L] and medial condyle femur [R/L] giving an overall score range of 0 to 6 (see [Appendix E](#)).

The proportion of subjects with enthesitis resolution, defined as LEI = 0 will be tested using pairwise stratified logistic regression as detailed in section 8.6.1.1 in the subgroup of subjects with LEI>0 at baseline. .

The change from baseline in LEI will be analyzed using the method described in 8.6.1.2, including only subjects with LEI > 0 at baseline. Descriptive summaries by treatment group and visit will also be displayed for Part A and Part B.

The SPARCC Index uses 18 sites, greater trochanter (R/L), quadriceps tendon insertion into the patella (R/L), patellar ligament insertion into the patella or tibial tuberosity (R/L), achilles tendon insertion (R/L), plantar fascia insertion (R/L), medial epicondyle (R/L) and supraspinatus insertion into greater tuberosity of humerus (R/L). The maximum score is 16.

The change from baseline in SPARCC will be analyzed using the method described in 8.6.1.2, including subjects with SPARCC > 0 at baseline. Descriptive summaries by treatment group and visit will also be displayed for Part A and Part B. For Part A and B there will also be an LOCF summary of the LEI and SPARCC to present the absolute, change from baseline and percent change from baseline by the randomized treatment arm.

#### **8.6.4.7 Bath Ankylosing Spondylitis Disease Activity Index (BASDAI)**

The BASDAI will be assessed at Week 4, Week 8, Week 12, Week 16, Week 20 and Week 24 however the secondary endpoint is the proportion of BASDAI responders at Week 12.

BASDAI response criteria is defined as:

- BASDAI Responder: *participant who had improvement in the BASDAI response criteria  $\geq$  50%;*
- BSDAI Non-responder: *Otherwise.*

The BASDAI is a validated composite index consisting of 6 participant numerical rating scales (NRS) to measure severity of the following:

- Fatigue;
- Axial involvement;
- Peripheral articular involvement;
- Localized tenderness/enthesopathy;
- Severity of morning stiffness;
- Time of morning stiffness.

Each NRS has a range of 0 to 10 where 0 represents “none” and 10 represents “very severe.” For Question 6, 0 represents no stiffness and 10 represents 2 or more hours of stiffness.

The composite BASDAI score is calculated as the average of questions 5 and 6 (Severity and time of morning stiffness), then as the mean of first 4 questions and the average of questions 5 and 6.

$$BASDAI = \frac{Q1 + Q2 + Q3 + Q4 + \frac{(Q5 + Q6)}{2}}{5}$$

A response rate of BASDAI is calculated as subjects with at least a 50% improvement in BASDAI.

A Non-responder imputation method will be used for all missing data as detailed in [Section 8.3.1](#).

The null hypotheses to be tested are that the proportion of BASDAI50 responders at Week 12 are no different for the following comparisons:

- sonelokimab 120 mg Q2W versus placebo

- sonelokimab 60 mg Q2W versus placebo
- sonelokimab 60 mg Q4W versus placebo

To test these hypotheses, a pairwise stratified logistic regression will be used as detailed in [Section 8.6.1.1](#). Descriptive summaries by treatment group and visit will also be displayed for Part A and Part B

The change from baseline in BASDAI will be analyzed using the method described in 8.6.1.2. Descriptive summaries by treatment group and visit will also be displayed for Part A and Part B.

### 8.6.4.8 Psoriatic Assessment Impact of Disease-12

The psoriatic assessment impact of disease-12 (PsAID-12) is self-administered by the participant and is a questionnaire including 12 health domains related to PsA. Each domain is evaluated on a score of 0 (None) to 10 (Extreme). The 12 domains are: pain, fatigue, skin problems, work and/or leisure activities, functional capacity, discomfort, sleep disturbance, coping, anxiety, embarrassment and/or shame, social participation, and depression (See Appendix F).

The PsAID-12 final value is calculated by summing each weighted domain which is calculated by multiplying the score (range of 0 to 10) by the weighted value as given in the table below and then dividing the total by 20:

| Domain NRS Value               | Multiplication |
|--------------------------------|----------------|
| Pain                           | 3              |
| Fatigue                        | 2              |
| Skin                           | 2              |
| Work and/or leisure activities | 2              |
| Function                       | 2              |
| Discomfort                     | 2              |
| Sleep                          | 2              |
| Coping                         | 1              |
| Anxiety                        | 1              |
| Embarrassment                  | 1              |
| Social Life                    | 1              |
| Depression                     | 1              |

A PsAID-12  $\leq 3$  responder is a subject who has a final value of 3 or below.

A Non-responder imputation method will be used for all missing data as detailed in [Section 8.3.1](#).

The exploratory null hypotheses to be tested are that the proportion of PsAID-12  $\leq 3$  at Weeks 4, 8 and 12 are no different for the following comparisons:

- sonelokimab 120 mg Q2W versus placebo
- sonelokimab 60 mg Q2W versus placebo
- sonelokimab 60 mg Q4W versus placebo

To test these hypotheses, a pairwise stratified logistic regression will be used as detailed in Section 8.6.1.1. Descriptive summaries by treatment group and visit will also be displayed for Part A, Part B and Part A+B.

The change from baseline in PsAID-12 will be analyzed using the method described in 8.6.1.2. Descriptive summaries by treatment group and visit will also be displayed for Part A and Part B. For Part A and B there will also be an LOCF summary of the PsAID-12 to present the absolute, change from baseline and percent change from baseline by the randomized treatment arm.

### 8.6.4.9 Leeds Dactylitis Index

The Leeds Dactylitic index (LDI) is assessed by an individual suitably qualified and experienced in the administration of the instrument. It measures the ratio of the circumference of the affected digit to the circumference of the digit on the opposite hand or foot, using a minimum difference of 10% to define a dactylitic digit. The ratio of circumference is multiplied by a tenderness score, using a modification of LDA which is a binary score (1 for tender, 0 for non-tender) (See Appendix G). If both sides are considered involved, or the circumference of the contralateral digit cannot be obtained, the number will be compared to data provided in the standard reference table for hands and feet.

The dactylitis count is the number of fingers and toes with dactylitis, ranging from 0 to 20.

The final total LDI score is calculated as:

$$[\{(A/B) - 1\} \times 100] \times C$$

where

A = Total circumference involved digit

B = Contralateral Digit

C = Tenderness Score

Descriptive summaries by treatment group and visit will also be displayed for Part A and Part B, including subjects with presence of dactylitis at baseline (LDI >0). In the final total LDI score calculation, only digits with >=10% difference from contralateral score will be included.

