#### 11.2.3.5 Leeds Dactylitis Index

LDI [Helliwell P.S. et al., 2005] will be assessed by an individual suitably qualified and experienced in the administration of this instrument, which may be the investigator or a qualified designee. This will occur at the visits indicated in the SOA in Section 3, Table 1.

The LDI basic measures the ratio of the circumference of the affected digit to the circumference of the digit on the opposite hand or foot, using a minimum difference of 10% to define a dactylitic digit. The ratio of circumference is multiplied by a tenderness score, using a modification of LDI which is a binary score (1 for tender, 0 for non-tender). If both sides are considered involved, or the circumference of the contralateral digit cannot be obtained, the number will be compared to data provided in the standard reference table for hands (Table 6) and feet (Table 7). This modification is referred to as LDI basic and will be applied in this study. The LDI requires a finger circumference gauge or a tape measure to measure digital circumference.

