##### Presence of dactylitis

If dactylitis is present with any finger or toe, the participant is counted as a participant with dactylitis.

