Appendix G: Leeds Diactylitis Score

[figure not shown]

| Finger / Toe | Circumference
Involved Digit (A) | Contralateral Digit
(or Tables) (B) | Tenderness Score
(C) | Final Score: $\frac{A}{B} \times C$ |
|--------------|-------------------------------------|----------------------------------------|-------------------------|-------------------------------------|
|              |                                     |                                        |                         |                                     |
|              |                                     |                                        |                         |                                     |
|              |                                     |                                        |                         |                                     |
|              |                                     |                                        |                         |                                     |
|              |                                     |                                        |                         |                                     |
|              |                                     |                                        |                         |                                     |
|              |                                     |                                        |                         |                                     |
|              |                                     |                                        |                         |                                     |
|              |                                     |                                        |                         |                                     |
| TOTAL        | 0                                   | 0                                      | 0                       | 0                                   |

Standard reference: Table - hands

| Digit  | Men | Women |
|--------|-----|-------|
| Thumb  | 70  | 58    |
| Index  | 63  | 54    |
| Middle | 63  | 54    |
| Ring   | 59  | 50    |
| Little | 52  | 44    |

Tenderness score: response to squeeze

0 no tenderness

1 tender

2 tender and wince

3 tender and withdraw

Table – feet

| Digit     | Men | Women |
|-----------|-----|-------|
| Great toe | 82  | 72    |
| Second    | 52  | 46    |
| Middle    | 50  | 44    |
| Fourth    | 50  | 44    |

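### The SAP's total LDI rule and its definition of B omit the reference-table comparator, so tender bilateral pairs within 10% of each other score zero if the text is followed as written

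*Combined protocol and SAP*

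**What the plan says.** The documents describe the LDI comparator in several places.

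- **Protocol 11.2.3.5**, repeated in the prose of **SAP 8.6.4.9**: "If both sides are considered involved, or the circumference of the contralateral digit cannot be obtained, the number will be compared to data" in the standard reference table. The protocol prints the values in Tables 6 and 7; the SAP reprints them in Appendix G.
- **SAP 8.6.4.9, threshold:** circumferences are compared "using a minimum difference of 10% to define a dactylitic digit".
- **SAP 8.6.4.9, formula:** [{(A/B) − 1} × 100] × C, with "B = Contralateral Digit" and no mention of the tables.
- **SAP Appendix G, score form:** the column for B is headed "Contralateral Digit (or Tables) (B".
- **SAP 8.6.4.9, closing rule:** "In the final total LDI score calculation, only digits with >=10% difference from contralateral score will be included".
- **SAP 8.6.4.9, subset:** the by-visit descriptive summaries are limited by "including subjects with presence of dactylitis at baseline (LDI >0".
- **Protocol 11.2.3.5, presence of dactylitis:** "If dactylitis is present with any finger or toe, the participant is counted as a participant with dactylitis". This does not depend on the LDI score.

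Change from baseline in LDI is listed among the other secondary endpoints (protocol 7.2.3, SAP 4.2).

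**The concern.** The reference table exists for the case in which the opposite digit is not a healthy control. The SAP states that provision, and then writes both the denominator and the rule for entering the total in terms of the opposite digit only. A programmer who codes the formula and the closing sentence as they stand would compare two swollen digits with each other, find little difference and drop both. Where the opposite digit cannot be measured, no contralateral difference exists, so that digit fails the rule as well.

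Two things are at stake. A participant whose only dactylitis is of this kind gets a baseline LDI of 0 and falls outside the LDI >0 subset, although the protocol counts that participant as having dactylitis. The score can also move the wrong way: when one of two similar swollen digits resolves, the other starts to qualify and the total rises from zero.

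**Working it through.** The plan states no figure for this rule, so there is none to reproduce. The check applies the SAP formula to example digit pairs.

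**Inputs.** Reference circumference for a man's index finger: 6.3 cm (protocol Table 6). Inclusion threshold: 10% (SAP 8.6.4.9). The circumferences are illustrative assumptions. Affected digits are tender (C = 1).

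**Formula.** Digit score = (A/B − 1) × 100 × C, summed over the digits that pass the 10% rule.

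**Three ways to code the text.**
- *Literal:* B and the 10% rule both use the opposite digit; only an excess of A over B counts.
- *Mixed:* B comes from the table when both sides are affected, but the 10% rule still looks at the opposite digit, in either direction.
- *Table:* B and the 10% rule both use the table value when both sides are affected.

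**Control case.** One affected finger of 7.56 cm opposite a normal, non-tender one of 6.3 cm: 7.56/6.3 − 1 = 20.0%, so 20.0 points under all three. The codings differ only when both sides are affected.

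| Pair (cm) | Above reference | Apart | Literal | Mixed | Table |
|---|---|---|---|---|---|
| 7.56 / 7.56 | 20% / 20% | 0% | 0 | 0 | 40.0 |
| 8.19 / 7.56 | 30% / 20% | 8.3% | 0 | 0 | 50.0 |
| 8.505 / 7.56 | 35% / 20% | 12.5% | 12.5 | 55.0 | 55.0 |
| 9.45 / 7.56 | 50% / 20% | 25.0% | 25.0 | 70.0 | 70.0 |

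The third row, step by step:
- Literal: 8.505/7.56 − 1 = 12.5%, so the larger digit scores 12.5. The smaller one is not larger than its comparator and scores nothing.
- Table: (8.505/6.3 − 1) × 100 + (7.56/6.3 − 1) × 100 = 35.0 + 20.0 = 55.0.
- Mixed: the smaller digit is 11.1% below the larger, so it passes a rule that counts either direction, and the total is again 55.0. If only an excess counted, the total would be 35.0.

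**Change over time.** Fingers of 7.6 and 7.2 cm are 20.6% and 14.3% above reference (7.6/6.3 and 7.2/6.3) but only 5.6% apart (7.6/7.2), so the literal total is 0. If the 7.2 cm finger returns to 6.3 cm, the other is 20.6% larger than its opposite and the total becomes 20.6. The score rises while the hands improve. With the table value as comparator while both are affected, the total goes from 20.6 + 14.3 = 34.9 to 20.6, which is the right direction.

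**Baseline subset.** A participant with the 7.56 / 7.56 pair and no other qualifying tender digit has LDI = 0 under the literal and mixed codings, so is not in the LDI >0 subset. A participant with another qualifying tender digit stays in it.

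**The case against.** The best defence is that the closing sentence only restates the 10% definition of a dactylitic digit. The SAP does not define what it means by a contralateral score. The same section gives the table rule, and Appendix G labels B as the opposite digit or the tables, so the phrase can be taken to mean whichever value serves as B. On that view nothing is lost. SAP section 9, which declares a changed BASDAI derivation, announces no change for LDI. That points to loose drafting, not a decision to abandon the protocol's rule.

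This has force as to intent: the documents do not establish that the sponsor means to exclude bilateral dactylitis. It does not rescue the text. Within the section, the contralateral digit is the opposite digit and the table is its substitute; Appendix G also names the two separately. The formula and the closing rule mention only the former. One section thus supports totals of 0 and 40 for the same hands.

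A reader might infer more than the text supports:
- *That all bilateral dactylitis scores zero, or that the table can never contribute.* Only pairs within 10% and digits without a measurable opposite are lost. A pair at 35% and 20% above reference scores 12.5 literally, and 55.0 when B comes from the table.
- *That some definite share of participants is affected.* The documents give no rate of dactylitis or of bilateral involvement.
- *That all LDI analyses use the restricted subset.* SAP 8.6.4.9 attaches it to the descriptive summaries. The general mixed-model provisions (protocol 12.3.3.2, SAP 8.6.1.2) carry no LDI >0 filter.
- *That the comparator should be fixed for each digit across visits.* Neither document says so, and it would override the protocol's rule once one side has resolved.

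**Conclusion.** The point holds as an internal contradiction: SAP 8.6.4.9 conflicts with its own prose, with Appendix G and with protocol 11.2.3.5, and its formula and closing rule are wrong as written. Taken literally, a tender pair within 10% of each other loses its whole score (40 points in the symmetric example), a digit with no measurable opposite is left out, and a more unequal pair can be understated (12.5 against 55.0).

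These sizes rest on assumed circumferences, C = 1 and the male index-finger reference; they show what the rule does, not how often it matters. How many participants would be affected, or would leave the baseline subset, cannot be estimated from the documents. LDI is an other secondary endpoint without confirmatory testing, so ACR50, ACR20, PASI90, the multiplicity procedure and the sample size are unaffected. The point is worth correcting because the present text can be programmed to give a wrong score.

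**What to change.** In SAP 8.6.4.9:

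1. Define B in the formula as the contralateral digit or, where both sides are involved or that digit cannot be measured, the sex- and digit-specific reference value.
2. Reword the closing rule so that a digit enters the total when A exceeds that same B by at least 10%.
3. Derive the baseline LDI >0 flag from the score so defined, and check it against the protocol's definition of presence of dactylitis.

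The cost is a few lines of SAP text and the matching derivation code. The reference values are already in both documents, and the score form already has columns for the circumferences, so no new data are needed.
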